### 2.14. Safety Assessment

AEs will be reported for every visit during the treatment period. The intensity and frequency of each event will be monitored. If serious AEs occur, postmanagement will be properly conducted. Local discomfort or pain, headache, fatigue, or referred pain can occur immediately after CMT but are usually mild and temporary.

### 2.15. Sample Size Calculation

RCTs evaluating the efficacy of a manual therapy, compared with placebo, for cervicogenic dizziness gave values for the mean changes and standard deviations [11, 13]. With 15.9 as the mean difference between the intervention and control groups and 12.91 as the standard deviation, the necessary sample size calculated using PASS 14 was 12 per group (two-sided, *α* = 0.05 and 1 − *β* = 0.9). We will allocate a total of 50 participants (25 per group), allowing for an anticipated drop-out rate of 40%.

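### The stated 12 per group gives about 82% power, not 90%, and 40% drop-out takes 12 to 20 per group, not the planned 25

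*Protocol article*

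**What the plan says.** The whole derivation is in section 2.15 of the protocol article. The inputs come from earlier trials: "RCTs evaluating the efficacy of a manual therapy, compared with placebo, for cervicogenic dizziness gave values for the mean changes and standard deviations". The effect and spread are given in the words "With 15.9 as the mean difference between the intervention and control groups" and "12.91 as the standard deviation", and the error rates as "two-sided, *α* = 0.05 and 1 − *β* = 0.9". The result is that "the necessary sample size calculated using PASS 14 was 12 per group". The enrolment step follows: "We will allocate a total of 50 participants (25 per group), allowing for an anticipated drop-out rate of 40" per cent.

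Section 2.16 names the two-sample t-test or the Wilcoxon rank-sum test for comparisons between groups. Section 2.2 sets a 1:1 allocation and the same total of 50.

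**The concern.** Three printed figures should form a chain: 90% power leads to a number per group, and that number with 40% drop-out leads to enrolment. The middle figure fits neither neighbour. A standardised difference of about 1.23 needs more than 12 per group for 90% power at a two-sided 5% level, and losing 40% of 25 leaves 15, not 12.

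The figure matters because the protocol calls it the necessary sample size for the primary comparison and expects heavy attrition. A reader who sees 12 complete patients per arm at the end would conclude that the trial had kept its 90% power. The per-protocol set in section 2.16 counts only participants who completed all interventions and assessments, so it is the analysis most likely to shrink towards that number.

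**Working it through.** **Inputs, all from section 2.15:** difference Δ = 15.9; standard deviation σ = 12.91; α = 0.05 two-sided; power 0.90; drop-out 40%; 25 per group enrolled. The test is the two-sample t-test of section 2.16 with equal groups.

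**1. Attempt to reproduce 12 per group.** The standardised difference is 15.9/12.91 = 1.2316. The normal approximation gives

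n = 2(z₀.₉₇₅ + z₀.₉₀)² (σ/Δ)² = 2(1.960 + 1.282)² (12.91/15.9)² = 13.85, so 14 per group.

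Even this formula, which understates the need in small samples, does not return 12.

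**2. Power of the t-test.** Power comes from the noncentral t distribution with 2n − 2 degrees of freedom and noncentrality Δ/(σ√(2/n)). At n = 12 the noncentrality is 15.9/(12.91 × √(2/12)) = 3.017, the degrees of freedom are 22 and the critical value is 2.074.

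| n per group | Power, two-sided 0.05 |
|---|---|
| 11 | 78.4% |
| 12 | 82.2% |
| 13 | 85.4% |
| 14 | 88.0% |
| 15 | 90.2% |
| 25 | 98.9% |

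Twelve is the smallest n with at least 80% power. Fifteen is the smallest with at least 90%.

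**3. Other readings that might give 12.**
- One-sided 5% test: 12 per group gives 89.9% by the t-test and 91.5% by the normal approximation, so a one-sided calculation could produce 12. The text says two-sided.
- Paired or one-sample test on the same inputs: 10 patients suffice (93.3%), and this is not the comparison between groups.
- Other inputs: 90% power with 12 per group needs Δ of about 17.9 or σ of about 11.5. Neither is printed.

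**4. Drop-out step.**
- 12/(1 − 0.40) = 20 per group, 40 in total.
- 12 × 1.40 = 16.8, so 17 per group, if the incorrect multiplicative rule was used.
- 15/(1 − 0.40) = 25 per group, 50 in total, exactly as planned.
- Going from 25 to 12 would be a loss of 1 − 12/25 = 52%, not 40%.

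Only 15 fits both the stated power and the stated enrolment.

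**The case against.** The strongest reply is that nothing that governs the conduct of the trial is wrong. Enrolment is 50 throughout the article. On the stated inputs 25 per group gives 98.9% power, and after the anticipated 40% drop-out 15 per group keep 90.2%. The protocol has no interim look or retention threshold tied to 12. The primary analysis uses the full analysis set with last observation carried forward, so most participants who leave early would still be analysed. An analysed sample of 12 per arm is thus unlikely in the primary analysis.

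All of that is fair, and it limits the consequence: the trial is not undersized on its own assumptions. It does not make the statement correct. The article prints every input and a result that does not follow from them, so this is an error and not a detail left out of a condensed text.

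A second reply is that 12 may come from a one-sided run and not from a misprint. The document cannot settle this, and the sponsor should look at the PASS output. Either way the text needs correcting, because it states a two-sided test.

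The source trials also had a placebo control, whereas here both arms receive active usual care. The article discloses the placebo comparison, and nothing in it shows by how much the difference would shrink. The arithmetic finding does not rest on this.

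**Conclusion.** The sample-size statement is wrong as written. Under its own inputs 12 per group gives 82.2% power, about 8 percentage points below the stated 90%; the type II error is about 18% instead of 10%. The requirement for 90% is 15 per group, and 15 is also the only figure that leads to 25 per group under 40% drop-out. Planned enrolment stands.

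This assumes a two-sample t-test with equal groups, a common standard deviation of 12.91 and a true difference of 15.9. With a Wilcoxon rank-sum test under normality the requirement rises slightly, to about 15/0.955 = 15.7, so 16 per group.

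**What to change.** Check the PASS output. If the two-sided 5% level and 90% power are intended, state in section 2.15 that 15 per group are needed (power 90.2%) and show 15/(1 − 0.40) = 25 per group, 50 in total.

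If 12 is to be kept with the present inputs and the two-sided test, state its power as 82% and the inflated number as 20 per group, and give a separate reason for enrolling 25. If 12 came from other settings, report those settings and derive the enrolment again.

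Optionally, add a sentence on sensitivity to a smaller difference against active usual care. As an illustration with the same standard deviation, an assumed 12 points gives 69% power with 15 per arm and 90% with 25; an assumed 10 points gives 54% and 77%.

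The main correction costs one or two sentences. Enrolment stays at 50, and the stated necessary number rises from 12 to 15 per group.

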### 2.16. Statistical Analysis

The full analysis set is defined as the group of participants who received CMT or UC and were assessed for the primary outcome at least once. The “per protocol” set is defined as the group of participants who completed all planned interventions and outcome assessments. Efficacy data will be analyzed primarily using the full analysis set and secondarily using the per protocol set. The missing data will be imputed using the “last observation carried forward” method. Safety data will be analyzed using the safety assessment set, which is defined as the group of participants who received CMT or UC at least once.

The primary and secondary outcomes will be statistically analyzed using two-sample *t*-tests or Wilcoxon's rank-sum tests for intergroup comparisons and paired *t*-tests or Wilcoxon's signed-rank tests for intragroup comparisons. Categorical variables from demographic data or AEs will be analyzed using the Chi-square test or Fisher's exact test.

An independent statistician ([name]) will analyze the data at *p* < 0.05 with SAS 9.4 software (SAS Institute Inc.).

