### 2.6. Dropout Criteria

Enrolled participants will be dropped if (a) the investigators detect ineligibility after random allocation, (b) participants withdraw consent for participation, refuse to receive CMT or UC, or are lost to follow-up, (c) serious adverse events or complications that need treatment are reported, or (d) the participants or investigators significantly violate the study protocol, including the criteria concerning concomitant medication.

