### 2.7. Randomization, Allocation, and Blinding

Random number sequences will be generated by an independent statistician ([name]) using SAS® 9.4 software (SAS Institute Inc., Cary, NC). The randomization will be block-stratified by the recruitment hospital to keep the numbers of each group similar throughout the study. The statistician will provide each hospital with sealed envelopes, in each of which a random number and an allocated group are written. Immediately after a participant is found to be eligible according to the screening process, a TKM doctor who will administer UC or CMT will open the next envelope in the sequence. Because this study is open-labeled to the investigators and patients, only the outcome assessors will be blinded. The outcome assessors will be TKM doctors different from those who administer CMT and UC. Only clinical emergency situations will allow breaking of the randomization code and blinding. At the end of the study, each outcome assessor will be asked which group he or she thought the patient was allocated to, and the answers will be used to calculate a blinding index (BI) [23].

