### 2.12. Outcomes

#### 2.12.1. Primary Outcome

*Dizziness Handicap Inventory (DHI). *The DHI is a patient-rated outcome (PRO) assessment that evaluates dizziness-induced impairments functionally, emotionally, and physically [30]. A Korean version of the scale has been validated [31]. The scale, consisting of 25 items with 4 points for each (scores 0–100), is frequently used for cervicogenic dizziness [2, 10–13]. The primary endpoint is defined as the mean difference of DHI total scores between day 0 and week 6. Subordinately, the intergroup effect at an intermediate time point (the mean difference between day 0 and week 3), as well as intragroup effects within each group, will be analyzed.

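### The primary efficacy set requires receipt of CMT or UC, so in this open-label trial a randomised patient who leaves before any session is excluded, and no stated efficacy analysis covers everyone randomised

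*Protocol article*

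**What the plan says.** Section 2.16 (Statistical Analysis) defines the full analysis set as "participants who received CMT or UC and were assessed for the primary outcome at least once". The per protocol set consists of those who completed all planned interventions and assessments. On the use of the two sets: "Efficacy data will be analyzed primarily using the full analysis set and secondarily using the per protocol set". On gaps in the data: "The missing data will be imputed using the “last observation carried forward” method".

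Section 2.7 (Randomization, Allocation, and Blinding) describes the masking: "Because this study is open-labeled to the investigators and patients, only the outcome assessors will be blinded". It also says that once a patient is found eligible, "a TKM doctor who will administer UC or CMT will open the next envelope in the sequence".

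Section 2.6 (Dropout Criteria) foresees, among other cases, that "participants withdraw consent for participation, refuse to receive CMT or UC, or are lost to follow-up".

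Section 2.12.1 (Primary Outcome) makes the DHI change from day 0 to week 6 the primary endpoint. It describes the instrument this way: "The DHI is a patient-rated outcome (PRO) assessment that evaluates dizziness-induced impairments functionally, emotionally, and physically". Table 1 schedules the DHI at V1, V2, V7 and V13.

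**The concern.** Leaving out randomised patients who were never treated is usually defended on the ground that leaving before treatment cannot depend on the arm. That defence needs the arm to be hidden. Here the doctor who will treat the patient opens the envelope, and the patient is not blinded either. Someone who hoped for manual therapy and draws UC alone can leave for that reason. So can someone who draws CMT and then wants no part of the study.

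If either happens before a first session, the groups compared in the primary analysis are no longer the groups that randomisation formed. A larger sample does not remove such a bias, and it cannot be repaired later if nobody sought those patients' outcomes. The outcome is also rated by the unblinded patient, so a preference for one arm could affect both staying and scoring. The trial calls itself pragmatic, which makes the effect of allocation the natural target.

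**Working it through.** **1. Who is excluded.** Set the definition in section 2.16 against sections 2.6, 2.7, 2.8 and 2.9.

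| Patient after the envelope is opened | Received CMT or UC? | In the primary set? |
|---|---|---|
| Allocated UC, leaves before any session | No | No |
| Allocated CMT, leaves before any session | No | No |
| Allocated CMT, declines CMT, takes UC | Yes (UC is given in both arms, section 2.9) | Yes, given one DHI |
| Either arm, drops out after session 1 | Yes | Yes, given one DHI |

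The receipt clause therefore removes only patients who leave with no session of anything.

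**2. The second condition.** The set also asks for at least one DHI assessment. The DHI is taken at V1 and V2. If a baseline score counts, the receipt clause alone excludes the first two kinds of patient. If a later score is required, further patients are lost.

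**3. Whether another analysis covers them.** The per protocol set is a narrower group. LOCF fills gaps for patients inside a set and cannot bring in those outside it. No stated efficacy analysis includes all randomised participants.

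**4. Time at risk.** Sections 2.8 and 2.9 plan 12 sessions, two per week over 6 weeks. In Table 1, V2 (day 0, random allocation) to V13 makes 13 − 2 + 1 = 12 visits. Twelve sessions in twelve visits suggests that session 1 takes place at V2. This is an inference, because the intervention rows of Table 1 carry no marks in the text at hand.

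**5. Size.** The plan gives no figure for untreated leavers, so there is none to reproduce. The inputs are 25 per group, an SD of 12.91 and a planned difference of 15.9 (all section 2.15). The following are assumptions: k leavers, all in one arm, whose mean DHI change would have differed by g from that of those who stay.

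Mean of all 25 = mean of stayers + (k/25) × g, so excluding the leavers shifts that arm's mean by (k/25) × g.

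With g = 12.91 (one SD):

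- k = 1: 1/25 × 12.91 = 0.52 points; 0.52/15.9 = 3%
- k = 3: 3/25 × 12.91 = 1.55 points; 1.55/15.9 = 10%
- k = 5: 5/25 × 12.91 = 2.58 points; 2.58/15.9 = 16%

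With g from 5 to 15 points, the range is 1/25 × 5 = 0.2 to 5/25 × 15 = 3.0 points.

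**6. Power.** With a two-sided t-test at 0.05, a difference of 15.9 and an SD of 12.91, power is 98.9% for 25 against 25. It is 98.5% with three patients removed from one arm and 98.0% with five removed. Bias is the issue here, not power.

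**The case against.** The strongest reply is that hardly anyone will be affected. If session 1 is given at the randomisation visit, a patient must leave between the opening of the envelope and a session on the same day. Nothing in the document suggests that 3 or 5 of 25 would do so. The anticipated 40% drop-out in section 2.15 is not evidence of it, since no share is given for loss before treatment. The refusal clause in section 2.6 also covers people who refuse after session 1, and they remain in the primary set. All of this stands. It limits the size of the problem but does not make the definition sound.

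A second reply concerns the remedy. Under LOCF, a leaver with only a day-0 DHI would enter as zero change, so widening the set does not by itself recover the true outcome. Those who withdraw consent may not be reachable at all. This also stands, and it is why the rewording needs follow-up with it.

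A reader might infer more than the text supports on three points:

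- **That declining manipulation leads to exclusion.** It does not if the patient takes UC. The text therefore does not support saying that the CMT group shrinks to those willing to be manipulated.
- **That patients may be analysed by treatment received.** Section 2.16 is silent on this, but an article may leave it to the full protocol or analysis plan. Sections 2.8 and 2.9 describe the groups by allocation.
- **That the bias favours CMT.** Losing UC patients who would have done badly flatters UC and shrinks the apparent effect. Losing UC patients who would have done well does the reverse. The document does not settle which is more likely.

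**Conclusion.** The point holds in a narrow form. The primary efficacy set, as defined, can drop randomised patients for a reason linked to their arm, and no stated efficacy analysis includes them. This is a definition that the article states, not a detail left to another document.

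The expected size is unknown and may be small. Under the one-SD assumption, 1 to 5 untreated leavers in one arm shift that arm's mean by 0.5 to 2.6 points (3% to 16% of the planned difference), with the sign open. Similar losses in both arms would partly or wholly cancel. The number of leavers, their concentration in one arm and their distance from those who stay are all assumed. The case for changing the text rests on the low cost of doing so, not on evidence of a large bias.

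**What to change.** In section 2.16, define the full analysis set as all randomised participants, analysed in the arm to which they were allocated, and delete the receipt condition for efficacy. This definition also removes the doubt over whether a baseline DHI is enough to qualify.

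Add that the week-3 and week-6 DHI will be sought by telephone or mail from participants who decline treatment but have not withdrawn consent to follow-up, so that they do not enter through LOCF as zero change. The DHI is a questionnaire, so this is feasible. Keep receipt of treatment as the basis of the safety set.

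The cost is a reworded definition, a few extra questionnaires and an effect estimate that may be diluted by patients who took no treatment.

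### LOCF is the only missing-data rule for the primary DHI comparison in a trial allowing for 40% drop-out; outside special cases it biases the estimate, and the planned 90% power does not describe that analysis

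*Protocol article*

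**What the plan says.** Section 2.16 gives one rule for missing outcomes: "The missing data will be imputed using the “last observation carried forward” method". It ranks the analysis sets: "Efficacy data will be analyzed primarily using the full analysis set and secondarily using the per protocol set". The full analysis set consists of participants "who received CMT or UC and were assessed for the primary outcome at least once"; the per protocol set consists of "participants who completed all planned interventions and outcome assessments". The between-group test is a two-sample t-test or a rank-sum test.

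Section 2.15 sizes the trial "With 15.9 as the mean difference between the intervention and control groups and 12.91 as the standard deviation", two-sided at 5% with 90% power, reports 12 per group, and continues: "We will allocate a total of 50 participants (25 per group), allowing for an anticipated drop-out rate of 40"%.

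Section 2.12.1 defines the primary endpoint as the DHI change from day 0 to week 6. Table 1 schedules the DHI at screening, day 0, visit 7 (week 3) and visit 13 (week 6) only.

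**The concern.** With this schedule, a patient without a week-6 DHI can be given only one of two values. A patient who leaves after week 3 is scored as if the mid-treatment value were the final one. A patient who leaves before week 3 is scored as unchanged, provided that the day-0 DHI is enough to enter the full analysis set. Neither value estimates the week-6 outcome unless nothing changes after the last assessment.

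At the planned drop-out rate, up to 20 of 50 primary outcomes could be carried values. If both arms lose patients equally, a real effect is diluted. If one arm loses more, ordinary improvement over time is credited unequally and can look like a treatment difference. The sample size calculation, by contrast, treats drop-outs as lost and powers the remaining patients for the full 15.9 points. It therefore describes a different analysis from the one in Section 2.16.

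**Working it through.** **The plan's own figure.** The normal formula is n = 2(1.960 + 1.282)² × (12.91/15.9)² = 13.9, so 14 per group; the exact two-sided t-test needs 15. The stated 12 is not reproduced (t-test power at 12 per group: 0.82), but that is a separate matter. For this point, 25 × 0.6 = 15 completers per group, with power 0.90 for an undiluted 15.9 points. The total of 50 thus supports 90% power for patients with an observed week-6 DHI.

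**Expected value under LOCF.** Let m be the mean week-6 improvement, p the drop-out proportion, e the share of drop-outs leaving before week 3, and f the share of improvement reached by week 3. With drop-out independent of outcome:

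- Baseline-only patients included: mean = m × [(1 − p) + p(1 − e)f]
- Baseline-only patients excluded: the same, divided by (1 − pe)

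**Inputs.** From the documents: 15.9, 12.91, 25 per group, p = 0.40 overall. Assumed, because the documents give no values: UC improves 5 points, f = 0.5, e = 0.5, and the week-3 and week-6 changes correlate 0.6 with equal SD.

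**Planned effect, equal drop-out.** The multiplier is 0.6 + 0.4 × 0.5 × 0.5 = 0.70.

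- Included: 0.70 × 15.9 = 11.1 points (30% low)
- Excluded: 0.70/0.80 = 0.875, and 0.875 × 15.9 = 13.9 points (12.5% low)

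**No true effect, both arms improving 15 points, drop-out 50% UC and 30% CMT (assumed).** The multipliers are 0.5 + 0.5 × 0.5 × 0.5 = 0.625 for UC and 0.7 + 0.3 × 0.5 × 0.5 = 0.775 for CMT.

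- Included: 15 × (0.775 − 0.625) = 2.25 points of false benefit
- Excluded: 15 × (0.775/0.85 − 0.625/0.75) = 13.68 − 12.50 = 1.18 points
- With 5 points of improvement instead of 15: 0.75 and 0.39 points
- With the two drop-out rates swapped, the sign reverses

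**Power and type I error.** Simulation of the two-sample t-test with 25 randomised per group, 20,000 runs per scenario. Where separate runs differed slightly, a range is given.

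| Scenario | Baseline-only included | Baseline-only excluded |
|---|---|---|
| 15.9-point effect, 40% drop-out in each arm, half early | 11.1 to 11.2 points, power 85% | 13.9 points, power 89% |
| Same, all leave before week 3 | 9.5 points, power 77% | no carried values |
| Same, all leave after week 3, half the change by then | 12.8 points, power 91% | same |
| Same, all leave after week 3, full plateau by then | 15.9 points, power 99% | same |
| No effect, both improve 15, UC 50% and CMT 30% | 2.2 to 2.3 points, type I error 9 to 10% | 1.2 points, 6 to 6.5% |
| No effect, both improve 5, same drop-out | 0.8 points, 5 to 6% | 0.4 points, 5% |
| No effect, both improve 15, equal drop-out | no bias, 5% | no bias, 5% |

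Completer estimates were unbiased with type I error near 5% in these runs, because drop-out was simulated as random.

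**The case against.** The strongest objection concerns the full analysis set. Section 2.5 requires a baseline DHI of at least 16, so every eligible patient already has a score. If that score counted, the condition of at least one assessment would exclude nobody. It also follows the words about receiving treatment, which suggests an assessment after treatment began. On that reading early leavers are excluded, no zero changes are imputed, and most of the distortion goes. This has force: it is not established that zero-change imputation will occur, and both columns of the table must be shown. What remains is that the text does not settle the question, and that week-3 values replace week-6 values on either reading.

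A reader might infer that unequal drop-out is likely because patients know their allocation and only one arm receives CMT. The documents do not support *likely*. Both arms attend 12 sessions on the same twice-weekly schedule (Sections 2.8 and 2.9), and no arm-specific rate is given. The drop-out criteria in Section 2.6, such as refusal of treatment or a concomitant-medication violation, make it possible and no more.

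The 40% is a planning allowance. Some of those patients may never be treated and so fall outside the full analysis set, which makes 20 of 50 a ceiling.

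Finally, a completer analysis is already planned. It is secondary, however, and the per protocol set also requires completion of all interventions, so it does not repair the primary estimate.

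**Conclusion.** The point holds in conditional form and should be fixed. LOCF as the sole rule gives a biased primary estimate except in special cases: drop-outs all leave after DHI has plateaued by week 3, or there is no effect and drop-out is equal. Bias also vanishes if neither arm changes at all, or if every drop-out leaves before week 3 and is excluded. Nothing in the documents gives grounds for relying on any of these.

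Under the stated assumptions the planned effect falls by 12.5% to 30%, depending on how the full analysis set is read. The inflated type I error of up to about 10% needs both unequal drop-out and sizeable improvement in both arms; with 5 points of improvement it stays near 5 to 6%. Trajectory, timing, correlation and the 50/30 split are assumptions.

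Two stronger conclusions are tempting and not supported. One is that the DHI effect is biased without qualification; the plateau and equal-drop-out cases contradict that. The other is that power must fall below 90%. The 90% simply belongs to a different analysis, and the simulated power of the LOCF analysis with equal drop-out ran from 77% to 99%.

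**What to change.** In Section 2.16, make the primary analysis a likelihood-based repeated-measures model of DHI at weeks 3 and 6, with treatment by visit and adjustment for day-0 DHI and hospital, and without single imputation. Multiple imputation is an acceptable alternative. Move LOCF to a sensitivity analysis. State whether the full analysis set requires a post-baseline DHI.

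The cost is revised wording and modest programming in SAS 9.4, which is already planned. No extra patients, visits or data are needed. With 15 completers per group, an analysis without carried values has power of about 0.90 for 15.9 points, and a model that also uses the week-3 scores should do about as well or slightly better. The downside is reliance on data being missing at random, which a delta-adjusted sensitivity analysis for patients without a week-6 DHI can probe. The absence of that analysis from the article is not itself a fault, since such detail may sit in a statistical analysis plan.

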### 2.1. Objectives and Hypothesis

This study is aimed primarily at exploring the therapeutic effect of adjuvant CMT for 6 weeks in male and female patients (20–70 years old) with cervicogenic dizziness, previously under usual care treatments. The null hypothesis is that the mean Dizziness Handicap Inventory (DHI) scores at baseline and at week 6 will be equal for the CMT and UC groups.

Second, the severity and frequency of cervicogenic dizziness after CMT or UC will be evaluated, along with other outcome measures. Differences between the two groups in neck pain, stress level, and quality of life (QoL) will also be assessed. The safety of CMT will be examined using adverse event (AE) reporting.

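### The primary DHI comparison is an unadjusted two-group test of change scores: valid, but it gives away precision by not modelling day-0 DHI and hospital

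*Protocol article*

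**What the plan says.** - **Endpoint (section 2.12.1).** "The primary endpoint is defined as the mean difference of DHI total scores between day 0 and week 6". Section 3 also describes the primary outcome as a change from baseline.
- **Test (section 2.16).** "The primary and secondary outcomes will be statistically analyzed using two-sample" t-tests or "Wilcoxon's rank-sum tests for intergroup comparisons". One sentence covers all primary and secondary outcomes. It names no covariate or stratum term, and no criterion for choosing between the two tests.
- **Randomisation (section 2.7).** "The randomization will be block-stratified by the recruitment hospital"; there are two hospitals (section 2.3).
- **Null hypothesis (section 2.1).** The mean DHI "scores at baseline and at week 6 will be equal for the CMT and UC groups".
- **Planning values (section 2.15).** "With 15.9 as the mean difference between the intervention and control groups and 12.91 as the standard deviation", from earlier trials that "gave values for the mean changes and standard deviations".

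**The concern.** The article names its method, and neither named test can adjust for a covariate or a stratum. Two variables that could sharpen the comparison are available for every patient: day-0 DHI and hospital. A change score uses the baseline with its coefficient fixed at 1. If the true regression slope of week-6 DHI on day-0 DHI is below 1, subtraction over-corrects. The extra noise stays in the estimate, and part of any chance baseline imbalance comes through with its sign reversed. Entry requires a DHI of at least 16, with no upper limit on a 0 to 100 scale, so baseline values may spread widely in arms of at most 25.

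Leaving out a stratification factor that predicts outcome gives a standard error that is too large. In a 50-patient trial, a smaller true effect than planned would then be more likely to be missed. That is a realistic case: the planning values come from placebo-controlled trials, whereas here both arms receive 12 sessions of physical therapy and education.

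Two smaller wording points belong with this. The t-test and the rank-sum test do not test the same hypothesis, and the article does not say which is primary. The null in section 2.1 also mentions equality at baseline, which is not the question that the trial asks.

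**Working it through.** **Inputs.** Difference 15.9, SD 12.91 (taken as the SD of change), two-sided α = 0.05, power 90%, 25 per arm, 40% drop-out, all from section 2.15. The correlation r between day-0 and week-6 DHI is not in the document, so a range of 0.3 to 0.7 is assumed. A difference of 10 points is also assumed, as an illustration of a smaller effect.

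**The plan's own figure.** The standardised difference is 15.9/12.91 = 1.232. A two-sided t-test with 90% power needs 14.88, so 15 per group (14 by the normal formula), not the stated 12. With 12 per group the t-test has 82% power. Because 15/(1 − 0.4) = 25, the planned 25 per arm matches 15 evaluable. The mismatch with 12 is a separate matter. The check below uses 15 per arm (25 × 0.6) and 25 per arm (nobody lost from the primary analysis).

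**Variance ratio.** Let σ² be the variance at both day 0 and week 6.
- Change score: 2σ²(1 − r)
- Week-6 DHI adjusted for day 0 (ANCOVA): σ²(1 − r²)
- Ratio: (1 + r)/2

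| r | Ratio | Variance reduction | Residual SD = 12.91 × √ratio |
|---|---|---|---|
| 0.3 | 0.65 | 35% | 10.41 |
| 0.5 | 0.75 | 25% | 11.18 |
| 0.7 | 0.85 | 15% | 11.90 |

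**Power** (noncentral t, 2n − 2 degrees of freedom):

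| Per arm | Difference | Unadjusted | r = 0.3 | r = 0.5 | r = 0.7 |
|---|---|---|---|---|---|
| 15 | 15.9 | 90% | 98% | 96% | 94% |
| 15 | 10 | 54% | 72% | 66% | 60% |
| 25 | 15.9 | 98.9% | >99% | >99% | >99% |
| 25 | 10 | 77% | 91% | 87% | 83% |

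Charging two degrees of freedom for the covariates lowers the adjusted 10-point figures at 15 per arm by about 0.2 of a percentage point.

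**Baseline imbalance, 15 per arm, r = 0.5.** Here 2σ²(1 − r) = σ², so σ = 12.91. The day-0 difference between arms has standard deviation 12.91 × √(2/15) = 4.7 points. A change score over-corrects by (1 − r) times the imbalance, so a one-SD imbalance moves the estimate by 0.5 × 4.7 ≈ 2.4 points.

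**Omitting hospital.** Simulated under the null: 24 per arm, two equal hospitals, arms balanced within hospital, nominal 5%. The type I error of the unadjusted t-test was about 5% with no hospital difference, 4.5% with a difference of 0.5 SD and 2.6% with 1 SD. The test becomes conservative.

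**Two named tests.** Simulated under the null with 15 or 25 per arm and normal, lognormal and t(3) data. Either test alone gave 4.0% to 5.2%, a choice by normality test gave 4.4% to 5.3%, and taking the smaller p-value gave 5.3% to 6.8%.

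**The case against.** The strongest reply is that nothing here is invalid. Under randomisation the change-score t-test is unbiased, and at the planning difference it reaches the 90% target with 15 per arm. The full analysis set with last observation carried forward keeps patients with at least one DHI assessment, so the primary analysis could approach 25 per arm. Unadjusted power at 15.9 points is then already 98.9%. The document gives no r, does not show that the hospitals differ, and nowhere mentions a 10-point effect. All of this stands. It limits the point to efficiency, and to effects smaller than planned. The ratio (1 + r)/2 also needs equal variances at the two visits; with unequal variances the slope can be 1 at some r below 1, and adjusting for baseline then gains nothing.

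A reader might infer three stronger things that the document does not support:
- **The baseline is thrown away.** It is not. A change score uses it, with a fixed coefficient.
- **The test will be picked after the data are seen.** The article gives no rule, but a statistical analysis plan that is not shown may hold one. The word joining the two tests may only match test to scale, since the same sentence covers the 0 to 5 dizziness frequency and the seven-option global perceived effect. A choice by normality test would cost almost nothing in type I error.
- **Ignoring the stratum produces false positives.** The effect runs the other way.

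The loose null in section 2.1 is likewise a matter of wording: sections 2.12.1 and 3 make clear that change is what will be compared.

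**Conclusion.** The point holds as one of lost precision and residual sensitivity to chance baseline imbalance. The planned test is valid, and conservative if the hospitals differ. At the planned 15.9 points the gain from adjustment is small: 4 to 8 percentage points of power with 15 per arm, and about 1 with 25. At an assumed 10 points it is 6 to 18 percentage points with 15 per arm and 6 to 14 with 25. These figures rest on equal variances at day 0 and week 6, on 12.91 being the SD of change, and on r between 0.3 and 0.7; any gain from modelling hospital is not counted. The missing rule for choosing between tests and the wording of the null are minor, and worth tidying in the same edit.

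**What to change.** In section 2.16, make the primary analysis one pre-specified linear model: week-6 DHI (or its change from day 0) on treatment, day-0 DHI and hospital. Report the adjusted mean difference with its 95% confidence interval. Use the same form for the continuous secondary outcomes that have a day-0 measurement; the global perceived effect is collected only at the last visit and has none. Keep the rank-sum test as a labelled sensitivity analysis. In section 2.1, word the null as no between-group difference in mean DHI change from day 0 to week 6.

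The cost is analysis wording only. Day-0 DHI and hospital are already recorded, and no visit, measurement or additional patient is needed. The change should be made before outcome data by group are available.
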